## Abstract

**Background:**

The case fatality for intentional self-poisoning in rural Asia is 10–30 times higher than in the West, mostly due to the use of highly toxic poisons. Activated charcoal is a widely available intervention that may – if given early – bind to poisons in the stomach and prevent their absorption. Current guidelines recommend giving a single dose of charcoal (SDAC) if patients arrive within an hour of ingestion. Multiple doses (MDAC) may increase poison elimination at a later time by interrupting any enterohepatic or enterovascular circulations. The effectiveness of SDAC or MDAC is unknown. Since most patients present to hospital after one hour, we considered MDAC to have a higher likelihood of clinical benefit and set up a study to compare MDAC with no charcoal. A third arm of SDAC was added to help determine whether any benefit noted from MDAC resulted from the first dose or all doses.

**Methods/design:**

We set up a randomised controlled trial assessing the effectiveness of superactivated charcoal in unselected adult self-poisoning patients admitted to the adult medical wards of three Sri Lankan secondary hospitals. Patients were randomised to standard treatment or standard treatment plus either a single 50 g dose of superactivated charcoal dissolved in 300 ml of water or six doses every four hours. All patients with a history of poison ingestion were approached concerning the study and written informed consent taken from each patient, or their relative (for unconscious patients or those <16 yrs), recruited to the study. The exclusion criteria were: age under 14 yrs; prior treatment with activated charcoal during this poisoning episode; pregnancy; ingestion of a corrosive or hydrocarbon; requirement for oral medication; inability of the medical staff to intubate the patient with a Glasgow Coma Score <13; presentation >72 hrs post-ingestion, and previous recruitment. The primary outcome was in-hospital mortality; secondary outcomes included the occurrence of serious complications (need for intubation, time requiring assisted ventilation, fits, cardiac dysrhythmias). Analysis will be on an intention-to-treat basis; the effects of reported time to treatment after poisoning and status on admission will also be assessed.

**Discussion:**

This trial will provide important information on the effectiveness of both single and multiple dose activated charcoal in the forms of poisoning commonly seen in rural Asia. If charcoal is found to be effective, it should be possible to make it widely available across rural Asia in an affordable formulation.

**Trial registration:**

Current Controlled Trials ISRCTN02920054

## Background

Deliberate self-poisoning is a major clinical problem in many parts of the developing world where highly toxic poisons and sparse medical facilities ensure a high fatality rate [1,2]. Pesticides are the major problem – the WHO estimates that they cause more than 220,000 deaths globally each year, of which most are due to organophosphorus (OP) insecticides [3]. But other poisons, in particular plants, other pesticides, and some pharmaceuticals are locally important problems [1].

Self-poisoning is particularly important in Sri Lanka where thousands of people die each year and preventing suicide has become a national public health priority [4,5]. The case fatality for self-poisoning in Sri Lanka is around 10%[1] but increases to over 50% for some pesticides [6]. More effective medical management is urgently required [7,8].

Current management of self-poisoning involves resuscitation and stabilisation of the patient, administration of antidotes where available, and gastric decontamination [9]. Mechanical forced emesis and gastric lavage are routinely used in Sri Lanka and other parts of Asia, despite little evidence for benefit [10,11]. Activated charcoal is available in some hospitals but is not routinely used in all, due to doubts about its effectiveness.

Animal and simulated human overdose studies have shown that a single dose of activated charcoal, if given soon after a poison is ingested, can reduce absorption of the poison [12]. The ability of charcoal to prevent absorption of poison falls off rapidly within one hour. Multi-dose regimens of charcoal may be effective much later for some poisons since the presence of activated charcoal in the intestine will interrupt the enterohepatic circulation [13,14] and may also draw poison out of the gut vasculature into the bowel [15].

At the time this RCT was designed, there had been no human studies of activated charcoal with clinically relevant outcomes. During 1997 and 1999, the American Academy of Clinical Toxicology and European Association of Poisons Centres and Clinical Toxicologists published reviews assessing the value of both single and multiple dose regimens of activated charcoal in acute poisoning [12,14]. Each position statement noted that they had been unable to find high quality studies with which to assess the clinical benefit of activated charcoal. The reports stressed the importance of establishing high quality RCTs with clinically relevant outcomes in order to determine the role of these interventions in poisoning management. The evidence for clinical benefit from a single dose of activated charcoal was again reviewed in 2004, but no new trials were reported [16].

We further carried out a *Clinical Evidence *search and appraisals in 2001 (and annually thereafter), together with systematic review of Medline, Embase, and Cochrane Collaboration databases, plus discussion with experts in the field, to identify relevant RCTs looking at activated charcoal in acute self-poisonings before starting our RCT [17]. We were unable to find any studies that were not discussed in the above reviews.

After this RCT started, two controlled studies of a single dose of activated charcoal in poisoning with pharmaceuticals were reported from the USA[18] and Australia [19]. Both used a primary outcome of length of hospital stay rather than a clinical outcome. The former study recruited 1479 patients but did not randomize them, instead using an 'even-odd day' system for allocation. A problem with this method is shown by the very different numbers of patients allocated to each arm, drawing doubt on the conclusion that activated charcoal had no effect. The latter study randomised 327 patients and found no difference between patients receiving charcoal and those receiving none. Neither study was relevant to the majority of patients seen in Sri Lanka.

15 months into the trial, a 400 patient RCT was published that reported benefit from 12 doses of activated charcoal in yellow oleander poisoning [20], a poison ingested by around 30% of patients in our RCT. After review of the published RCT and the results of an interim analysis of 595 oleander poisoned patients receiving either SDAC or MDAC in this trial, the IDMEC decided that it was important to obtain independent verification of the first study's result, and recommended that the trial continue.

We set up this RCT in Sri Lanka in early 2002 and recruited the first patient on the 31^st ^March 2002. The study was stopped in October 2004 after the final interim analysis with more than 4500 patients recruited. The final data analysis is underway and should be reported during 2007.

## Methods/design

The study was designed as an open RCT with three parallel groups: multiple dose charcoal vs single dose charcoal vs no charcoal in Sri Lankan adult patients presenting to a secondary hospital with a history of acute self-poisoning. From May 2004, an RCT of pralidoxime in symptomatic organophosphorus pesticide poisoned patients (ISRCTN55264358) was nested into this study.

The principal research question to be addressed was whether activated charcoal, either as a single or multi-dose regimen, will reduce the rate of death and complications following acute poisoning.

The trials were drawn up using the MRC's clinical trial proforma and were designed to be compliant with the CONSORT statement [21].

### Patients

The RCT was performed in Anuradhapura and Polonnaruwa General Hospitals, the secondary referral hospitals in North Central Province, and in Kurunegala Teaching Hospital, the secondary referral hospital for much of the North Western province and a tertiary referral hospital for areas further north.

All patients with a history of poison ingestion were approached concerning the study. Written informed consent was requested from conscious patients by a study physician in the patient's own language. For patients between 14 and 16 years, written informed consent was obtained from the patient's parents/guardian. As requested by the Faculty of Medicine Ethics Committee (see below), consent for unconscious adult patients was sought from accompanying relatives. Patients under the age of 16 or unconscious on admission and without any relatives were not recruited to the trial.

Patients who do not give consent to recruitment received usual care from the medical ward staff. Their progress was monitored at each ward round but the study team was not involved in their care.

### Inclusion and exclusion criteria

The study aimed to recruit all patients admitted to the adult medical wards of the study hospitals with a history of acute oral self-poisoning. Exclusion criteria were: age under 14 yrs (lower age of patients admitted to Sri Lankan adult medical wards); prior treatment with activated charcoal during this episode of poisoning; known pregnancy; ingestion of a corrosive; ingestion of a hydrocarbon alone; requirement for oral medication; inability of the medical staff to intubate the patient with Glasgow Coma Score (GCS) <13; presentation >72 hrs post-ingestion, and previous recruitment to the RCT. The last four exclusion criteria were added to the protocol in an amendment submitted to the ethics committee in May 2002.

### Patient management

All patients are seen on admission to the medical wards or, in Kurunegala, after admission to the Emergency Treatment Unit (emergency department). There the patients were resuscitated as necessary by wards doctors together with study doctors. The patient's airway was stabilised and oxygen, atropine, fluids, and antidotes given as necessary.

Gastric decontamination was only started when patients were stable. The original protocol stated that patients would receive neither gastric lavage nor forced emesis. However, at the request of the consultant physicians caring for the patients, from June 2003 patients who presented within two hours of ingestion of a potentially serious poison received a brief gastric lavage (3 × 300 ml of water). Many patients received either gastric lavage or mechanical forced emesis in the peripheral hospital transferring the patient before admission to the study hospitals.

Patients remained under the care of the hospitals' consultant physicians using management protocols agreed between the consultants and study team [22]. The ward medical teams made decisions about intubation and transfer of patients to intensive care or for cardiac pacing independently of study doctors. All decisions were made on the basis of clinical condition and do not reflect the poison ingested or the charcoal allocation.

Patients were seen regularly by full time study doctors at least every three hours and more often according to clinical need, 24 hrs a day. Patients were also seen on a study ward round twice each day (0830, 2030) at which time their condition was recorded in a handheld computer using a specially written database. Significant events (intubation, seizures, death) were recorded at the time of the event. The patients' condition over the previous 12 hrs was reviewed at each ward round.

Patients were first managed on the medical ward. Seriously ill patients, as judged by the medical team, were then transferred to the intensive care unit (ICU) as a bed became available. Each hospital had 2–8 ICU beds for medical patients; many were filled with OP poisoned patients and there was usually a delay in obtaining a bed.

Criteria for intubation included tidal volume less than 180 ml/breath using a Wright's respirometer, respiratory rate of less than 10 breaths/minute, abdominal breathing, or failure of non-invasive methods to maintain a patent airway. Arterial blood gas measurements were not available to guide therapy. Hypotensive patients, unresponsive to atropine and fluid resuscitation, were treated with dopamine plus dobutamine as necessary (these were the only inotropes available in the hospitals).

### Trial interventions and study procedures

Patients randomised to single or multiple dose activated charcoal regimens ingested 50 g of superactivated charcoal (Carbomix BP, Norit, NL; 2000 m^2^/g) in 300 ml of water (without sorbitol or mannitol) soon after recruitment. Patients receiving multiple doses subsequently ingested another five doses of 50 g charcoal at four hour intervals. The original RCT protocol proposed administering 18 doses of charcoal every 4 hours over 3 days. Early experience in the study demonstrated the immense difficulty of giving so many doses to patients (in particular gaining the patient's acceptance) and the number of doses was reduced to six in an amendment sent to the ethics committees in May 2002.

Alert patients drank the charcoal; patients with reduced consciousness received the charcoal via a nasogastric tube. Control patients did not receive activated charcoal. All patients were kept well hydrated to reduce the risk of intestinal blockage with the charcoal and monitored regularly throughout their time on the medical ward. Patients were followed up until final hospital discharge or transfer to a psychiatric ward.

We did not expect a major problem with compliance since the charcoal was given by the study team while the patient was under supervision in hospital. Unconscious patients received the charcoal by nasogastric tube after intubation. Conscious patients were actively encouraged to drink the charcoal by the study team; however, patients were not forced in any way to take the charcoal.

A 10 ml blood sample was taken using a sterile syringe and needle from each patient on recruitment. Further 5 ml blood samples were taken at one, four and twelve hours post-treatment, and then at daily intervals until discharge or death. Whether a needle or indwelling cannula was used was determined by the wishes of the patient. The identity and blood concentration of the poison was assayed retrospectively in only a subset of patients due to limited laboratory facilities.

### Randomisation

Patients were randomised into one of three study arms. The random allocation sequence was generated by computer and incorporated into a Microsoft Access programme written for patient recruitment, randomisation and event recording (Figure 1). Stratified block randomisation was performed using the following strata: (i) the toxin stated to have been ingested (oleander, organophosphate or carbamate, organochlorine, other pesticide or unknown pesticide or paraquat, medicine or unknown) ; (ii) reported time between poisoning and recruitment (<1 hr; 1–4 hrs; >4 hrs; unknown); and (iii) status on admission (Asymptomatic, Symptomatic with GCS 14 or 15/15, Symptomatic with GCS <14).

**Figure 1 F1:**
[figure not shown]
The hand held computer used to recruit and randomise patients and to record all events. Randomisation was performed at the patient's bedside. Allocation could not be predicted by the study doctor.

The allocation sequences were generated independently by the study statistician (EJ) and implemented by the programmer (SA), neither of whom had a role in patient recruitment, treatment or assessment. Variable block sizes of 3, 6 and 9 were used to allocate patients in equal numbers to each treatment group i.e. ratio 1:1:1 using Stata v7 software (ralloc subroutine version 3.2.5).

Participants were recruited and randomised by a study doctor at the bedside using a dedicated handheld computer at each study hospital (Figure 1). Randomisation occurred after the patient's baseline data had been entered and receipt of consent noted, and could not be manipulated by study doctors. The recruiting doctor was unable to predict allocation before randomisation.

All practical steps were taken to avoid bias: (i) the randomisation program was designed to be rapid and simple to operate, and yet remain independent of the investigators; (ii) the next treatment allocation could not be predicted in advance; (iii) the primary outcome, vital status at discharge, was unambiguous, and the secondary outcomes were objective; (iv) all outcomes were recorded systematically by the study team, not other hospital physicians; (v) patient follow-up was expected to be near 100% complete; and (vi) the analysis will be performed on an intention-to-treat basis.

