### Sample size

In both hospitals, at least 10% of poisoned patients die before discharge [1]. An absolute reduction of 3% will be clinically important. In order to be able to detect whether either regimen of activated charcoal reduced the death rate from 10% to 7%, with a significance level (alpha) of 5% and a power of 80%, a minimum of 1400 patients had to be recruited to each arm of the trial (i.e. 4,200 patients in total).

Sample size calculations were based on current practice and a case fatality rate of 10%. The Independent Data Monitoring and Ethics Committee (IDMEC) was asked to review the recruitment and event rates during the first year of the trial in order to make recommendations about expanding the trial by including further hospitals if necessary.

There should have been no loss to follow up for the primary outcome. Patients were either discharged alive from the wards or their bodies transferred to the morgue for judicial autopsy. All secondary outcomes were assessed in hospital before discharge.

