### Statistical analysis

The main analysis will be carried out on an intention-to-treat basis, using the chi -squared test for the primary outcome (or Fisher's exact test if appropriate) and for other dichotomous outcomes. Odds ratios (plus 95% confidence intervals) will be reported to establish magnitude and direction of the treatment effect. In the original protocol, we indicated that risk would be the chosen measure of effect; however, in order to be able to adjust the treatment effect estimate for stratification variables in future analyses, we will calculate odds instead, using logistic regression. Since the primary outcome is an uncommon event, risk and odds should be similar.

For outcomes where time-to-event is recorded, we will use the logrank test to compare treatment groups, produce Kaplan-Meier curves to illustrate the comparison, calculate incidence rates and perform Cox's regression to estimate hazard ratios, adjusted for stratification factors.

An analysis of trends in treatment effect for factors 'reported time from ingestion to treatment' and 'patient status on admission' will be performed.

It is possible that both treatment regimens, if effective in reducing case fatality rates, will be more effective the earlier they are started. Therefore we will assess the trends in clinical effectiveness according to time post-ingestion to start of therapy using statistical modelling techniques. In order to determine whether treatment should be started irrespective of severity, we will likewise also assess trends in case fatality rates across a gradient of severity.

Admission blood samples will be retrospectively analysed to determine the identity of the poison ingested. The primary analyses will be repeated using the confirmed identity of the poison.

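### Each hospital randomised on its own handheld, yet hospital is not a listed stratum and so drops out of the stratification-adjusted models; the cost is a little power, not bias

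*Protocol article*

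**What the plan says.** The Randomisation section opens its list with "Stratified block randomisation was performed using the following strata: (i) the toxin stated to have been ingested" and adds reported delay and status on admission. Those are the only three factors. In the text after Figure 1 of the same section, "Participants were recruited and randomised by a study doctor at the bedside using a dedicated handheld computer at each study hospital". The article does not say whether each device held its own allocation sequence.

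The Statistical analysis section plans a chi-squared test (or Fisher's exact test) for death and the other dichotomous outcomes. It prefers odds to risks so that logistic regression can later adjust for the stratification variables. For time-to-event outcomes it will use the logrank test and "perform Cox's regression to estimate hazard ratios, adjusted for stratification factors". No analysis in the article names hospital.

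The hospitals are not alike. Under Patients, two are secondary general hospitals and Kurunegala is a teaching hospital with a partly tertiary role. Under Patient management, Kurunegala patients are seen after admission to its emergency unit and the others on the ward; "Each hospital had 2–8 ICU beds for medical patients"; and the ward teams decide on intubation and transfer independently of the study doctors.

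**The concern.** Hospital is a plausible predictor of intubation and of time to first ventilation, because case mix, route of entry, bed supply and the deciding team can all differ between sites. Such a factor normally belongs in an adjusted analysis, and more so if it was part of the randomisation. Here the adjustment set is defined by reference to the strata, and hospital is not among them.

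The consequence depends on a fact that the article leaves open:

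- **Each handheld ran its own blocks.** Hospital was then in effect a fourth stratum. The arms are balanced within hospital, but an analysis that ignores hospital does not credit that balance, so its tests are conservative when hospital rates differ.
- **The sequences ignored hospital.** The arms are then balanced within hospital only in expectation. Unadjusted tests keep their level, but some precision that adjustment would recover is lost.

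In both cases what is at stake is efficiency in the adjusted and time-to-event analyses.

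**Working it through.** **Inputs from the article.** Strata of 5 toxin groups, 4 delay groups and 3 status groups; blocks of 3, 6 and 9; allocation 1:1:1; death rates of 10% versus 7%; alpha 5%; power 80%; 1,400 per arm (4,200 in total).

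**Assumptions.** Hospital event rates and hospital shares are not given. The rates below are a range chosen for illustration. The shares in the simulation are 40/25/35%.

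**1. The plan's own figure.** For 10% versus 7%, two-sided 5% and 80% power, the two-proportion formula gives 1,356 per arm without and 1,422 with continuity correction. The stated 1,400 lies between them and gives 81.3% power uncorrected. The sample size is not in question.

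**2. Cells.** The listed strata give 5 × 4 × 3 = 60 cells, on average 4,200/60 = 70 patients each. With hospital there would be 180 cells, on average 23.3 each.

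**3. Share of outcome variance between hospitals (equal sizes).** Share = 1 − mean[p(1 − p)] / [p̄(1 − p̄)].

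- Death at 6/10/14%: p̄ = 0.10 and p̄(1 − p̄) = 0.0900. The within-hospital mean is (0.0564 + 0.0900 + 0.1204)/3 = 0.0889. Share 1.2%; standard-error ratio √(0.0900/0.0889) = 1.006.
- Intubation at 10/20/40%: p̄ = 0.233 and p̄(1 − p̄) = 0.1789. The within-hospital mean is (0.09 + 0.16 + 0.24)/3 = 0.1633. Share 8.7%; ratio 1.047.

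These ratios apply to a risk difference. With per-device sequences they show how far the unadjusted standard error is overstated. With sequences that ignore hospital, the unadjusted standard error is right, and the share is the variance that adjustment could remove.

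**4. Simulation.** 4,200 patients in three arms, 60 strata, permuted blocks of 3/6/9, 1,500 replicates per scenario, multi-dose versus control. Entries are the percentage of rejections, unadjusted / hospital-stratified Mantel-Haenszel. The odds ratio is (0.07/0.93)/(0.10/0.90) = 0.677.

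| Hospital rates | Odds ratio | Sequence per hospital | Sequence ignoring hospital |
|---|---|---|---|
| 10/10/10% | 1 | 4.7 / 4.8 | 5.4 / 5.4 |
| 7/10/13% | 1 | 5.7 / 5.8 | 5.8 / 6.0 |
| 5/10/20% | 1 | 5.3 / 5.7 | 4.6 / 5.2 |
| 5/20/40% | 1 | 3.1 / 4.1 | 4.6 / 5.2 |
| 7/10/13% | 0.677 | 81.2 / 81.5 | 79.9 / 80.2 |
| 5/10/20% | 0.677 | 83.7 / 84.6 | 83.2 / 85.1 |

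Monte Carlo error is about 0.6 points for type I error and √(0.83 × 0.17/1,500) ≈ 1.0 point for power. Both tests use the same simulated data, so their difference is less noisy than that. Under no effect the mean arm difference was 0.00 to 0.08 percentage points in every scenario. The mean worst within-hospital departure from an even split was 0.5 points with per-hospital sequences and 1.7 without.

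**5. Check on the 3.1%.** With shares 40/25/35% and rates 5/20/40%, p̄ = 0.21 and p̄(1 − p̄) = 0.1659. The within-hospital mean is 0.4 × 0.0475 + 0.25 × 0.16 + 0.35 × 0.24 = 0.143. The unadjusted z-statistic then has standard deviation √(0.143/0.1659) = 0.928, and the real level is 2[1 − Φ(1.96/0.928)] ≈ 3.5%, in line with the simulation.

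**6. Logistic scale.** At 10/20/40% the per-patient variance factor of the log odds ratio is 1/0.1789 = 5.59 without hospital and 1/0.1633 = 6.12 with it. Its standard error therefore rises by √(6.12/5.59) − 1 ≈ 4.7%. The conditional odds ratio also moves away from 1, so the gain appears as power and not as a shorter interval.

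**The case against.** The strongest reply is that nothing here is contradictory. Three strata are named, the Cox models adjust for them, and further covariates are not forbidden; a full analysis plan, not shown, may already include hospital. This reply is fair in part. But the article does not leave the adjustment set open: it names a rule, and the rule excludes hospital.

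A second reply is that much of any hospital difference may be case mix, which toxin, delay and status already capture. This stands. The figures above treat hospital as independent of those factors, so the gain over models that already adjust for them could be smaller.

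Some stronger readings are tempting but not supported:

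- **Distorted arm comparisons.** A reader might infer that site differences contaminate the treatment effect. Randomisation makes the arms comparable in expectation under either mechanism, and chance imbalance is already covered by the test's error rate.
- **Site-specific transfer practice.** The Outcomes section says that transfer followed the same criteria as anti-digoxin Fab. Patient management gives common intubation criteria and agreed management protocols. Variation in intubation and ventilation remains plausible, because local teams decided and ICU capacity differed, but it is not documented.
- **A different death rate at the third site.** The Sample size wording, "In both hospitals, at least 10% of poisoned patients die before discharge", concerns a planning assumption. It gives no evidence about randomisation or adjustment.
- **Adjustment of the main tests.** Death, intubation and Fab or transfer are first tested by unadjusted chi-squared. The stated adjustment concerns the Cox models and the later logistic models.

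**Conclusion.** The point holds as a minor improvement. Hospital is missing from the listed strata and therefore from the stated adjustment set, although each site had its own randomisation device and the sites differ in ways that could affect intubation and ventilation. There is no bias and no meaningful inflation of type I error. Under the assumed rates, omitting hospital costs at most about 2 points of power (83.2% versus 85.1%), and 0.3 points when rates are 7/10/13%. Conservatism appears only if each device ran its own sequence and hospital rates differ very strongly. For death the effect is small: about 1.2% of variance at an assumed 6/10/14%. All these sizes rest on assumed hospital rates and shares, and the article does not settle which randomisation mechanism applied.

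**What to change.** State whether the allocation sequences were generated separately for each hospital. In either case, add hospital (three levels) to the factors in the adjusted logistic models, and use it as a stratum in the Cox models and the logrank test. The benefit is likeliest for intubation and time to first ventilation. Describe the logistic gain as power. The unadjusted chi-squared test of death can stay as planned, and a treatment-by-hospital interaction test is not required.

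The cost is two parameters in the logistic models, with more than 4,500 patients recruited, and no new data, since patients were recruited on a hospital-specific device. Because recruitment has ended and the final analysis is under way, record the date of the change and report the adjusted results beside the unadjusted ones.
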